### 2.3.3 ASSESSMENT OF POTENTIAL RISKS AND BENEFITS

The main risks associated with this protocol are associated with the administration of oral ondansetron. Study questionnaires are designed to minimize questions which may be perceived as intrusive. To minimize risk associated with the administration of multi-dose ondansetron, the study inclusion and exclusion criteria were carefully selected to avoid known contraindications. Patients who have a known hypersensitivity or allergy to ondansetron or other serotonin receptor antagonist, a history of prolonged QT syndrome or presence of heart disease or arrhythmia, as well as individuals taking SSRI, SNRI, apomorphine, macrolide antibiotics or any medication accepted as causing torsades de pointes will be excluded from participation in the study.

Study medication will be administered at home by the participants' caregiver on an 'as needed' basis. Doses will be based on the weight of the participant at time of enrollment. Trained study research staff will calculate the appropriate dose of study medication to be administered. The dose information will be recorded on discharge instructions provided to the caregiver and the volume of study medication will be marked on a syringe to minimize measuring errors. Research staff will provide one-on-one teaching and printed instructions on how to administer the doses to the participant prior to participant discharge from the ED to minimize the risk of incorrect dosing.

Participants will be contacted 24, 48, and 168 hours (7 days) after randomization to obtain outcome endpoint data and determine if there have been any adverse events (e.g. diarrhea, constipation, headache, etc.). Data regarding ongoing vomiting, diarrhea, and/or fever, and return to healthcare will be collected during scheduled follow-up calls/emails. Caregivers can also provide general information regarding the child's illness or any other symptoms the child may be experiencing when completing the scheduled follow-up questionnaires. This information will be reviewed by a trained research team member for any possible adverse events or symptoms that may require medical care.

## 3 OBJECTIVES AND ENDPOINTS

The primary objective is to determine if the use of multi-dose oral ondansetron compared with placebo, provided at ED discharge, will result in improved outcomes in children treated in an Emergency Department for vomiting secondary to acute gastroenteritis.

The primary outcome is the development of moderate-severe disease in the 7 days after the index ED visit as measured by the MVS. The original 20 point Vesikari Score has been employed as a dichotomous variable in many clinical studies despite limited evidence supporting its use. However, it has been shown to correlate with other meaningful measures such as caregiver anxiety, helplessness, and stress. Recently, increasing severity scores were associated with higher caregiver worry, greater changes in the child's behavior, and trends towards greater impact on the caregivers' daily activities and higher caregiver distress. Moreover, two large multi-centre ED based RCTs have used the MVS as primary outcomes, both published in the New England Journal of Medicine in November 2018.

**Characteristics of the MVS:** We prospectively evaluated the MVS in an 11 centre (455 children) ED study which found that it effectively measures global disease severity. Factor analysis revealed that item correlations were acceptable and supported the appropriateness of retaining all factors. Multi-collinearity was not a problem and the correlations between the MVS and other measures of clinical significance were in the expected direction. Disease severity was associated with prolonged daycare ( $P = 0.01$ ) and work ( $P = 0.002$ ) absenteeism. The MVS had a normal distribution with minimal kurtosis ( $-0.14$ ; SE: 0.24) and skewing (0.39; SE: 0.12). There was good variation

across severity ranges (49% mild; 21% moderate; 30% severe). Variation between institutions was insignificant ( $P = 0.11$ ) and complete follow-up was achieved in 91% of participants.

**How will it be calculated?** Once follow-up is complete (Day 7), each variable is assigned a score for the entire study period (Time 0 to Day 7). Each participant gets a single total score for the study. Variables are scored based on the worst 24 hour period (e.g. maximal number of episodes of vomiting in a 24 hour period), the total duration of symptoms (e.g. number of days of vomiting), or are based on the occurrence of an outcome (e.g. hospitalization).

**What if at baseline the pre-enrollment MVS is  $\geq 9$ ?** Regardless of the score assigned at Time 0 (i.e. *pre-enrollment score*), EVERYONE reverts to a score of 0 at enrollment (i.e. the study evaluates the impact on the disease process going forward). The *pre-enrollment score*, which is based on symptoms prior to presentation, will serve as a covariate in a secondary analysis of the primary outcome and will be employed for sub-analysis purposes. **The primary outcome (the presence of moderate-severe disease, as defined by a MVS of  $\geq 9$  during the 7 day follow-up period) will ONLY include symptoms and outcomes that occur following the ED visit (i.e. after enrollment) and will not be directly impacted by the pre-enrollment score.**

**Why a cut-point of 9?** With the original score, severe disease was defined as  $\geq 11$ ; moderate as  $\geq 9$ . In our derivation study, construct validity was proven by using scores of  $\geq 9$  to define moderate and  $\geq 11$  to define severe disease. These cut-points were associated with significant increases in other measures of disease severity [e.g. daycare ( $P=0.01$ ) and work absenteeism ( $P=0.002$ )].

Outcome measure data will be collected using participant follow-up questionnaires performed 24, 48, and 168 hours (7 days) after enrollment (Time 0 = consent date and time). At the enrollment visit (Day 0), all caregivers will be asked their preferred method of communication for follow-up: email or telephone. Following discharge from the ED, trained study staff will contact caregivers for the duration of the follow up period as outlined in Section 1.3 SoA. The questionnaire (performed via telephone or secure web based link) will inquire about ongoing symptoms, medical evaluations, treatments, child care, resource utilization, and side effects. If speaking by telephone, detailed questioning will follow positive responses. The web based questionnaire will employ advanced logic to enhance ease of use. If the caregiver does not complete the online questionnaire within 24 hours, a telephone follow-up will be performed by study staff to obtain outcome data. Final data points will be collected from the caregiver after 168 hours (7 days). The follow-up questionnaire will also assess study intervention administration (ondansetron oral solution) at the 24 and 48 hour follow-up assessments. The study team will closely track how many doses the caregiver administered to the child by ensuring the questionnaires are completed in full. If the email questionnaire is not completed in full, a telephone call will be performed to obtain the missing data. If electronic follow-up is chosen, if the questionnaire is not completed within 24 hours of receipt, the study team will switch to phone follow-up to maximize the response rate and minimize recall bias.

The **presence and frequency of vomiting** will be measured following enrollment in the study using follow up questionnaires 24, 48, and 168 hours (7 days) after Time 0. Questionnaires (telephone or email) will contain questions regarding vomiting presence, number of episodes, and vomiting cessation date and time. In previous work, we have concluded that vomiting frequency is a predictor of outcomes in AGE.

**Return visits for unscheduled care** to a health care provider related to vomiting, diarrhea, dehydration, fever, abdominal pain, or fluid refusal within 7 days, not including scheduled visits (e.g. reassessments, vaccinations), will also be measured using follow up questionnaires 24, 48, and 168 hours (7 days) after Time 0. Questionnaires will ask caregivers if they brought their child to a health care provider for an unscheduled visit related to the current illness. If a return visit occurred, further questions will be asked related to **Intravenous (IV) insertion**, treatment course, and disposition. Return to care data will be confirmed by reviewing the participant's hospital chart, where

possible. This outcome is important as > 50% of children have a follow-up office visit, 8-18% require an ED visit, and 5-8% are hospitalized.

A **5-point Likert scale will be used to determine caregiver satisfaction** with the therapy provided (ondansetron or placebo oral solution) in the 48 hours following Enrollment in the study.

The following **secondary safety endpoints** are important as they will add more information about the secondary objective. The safety endpoints will include:

- 1) Serious Adverse Events (SAEs)
- 2) Frequency of diarrheal episodes during the 48-hours following ED disposition
- 3) Maximal number of diarrheal episodes in 24 hours
- 4) Palpitations
- 5) Pre-syncope/syncope
- 6) Chest Pain
- 7) Arrhythmias

All safety end point data will be obtained via participant follow-up questionnaires performed 24, 48, and 168 hours (7 days) after enrollment (Time 0). **Frequency and maximal number of diarrheal episodes** will be obtained by asking about presence of diarrhea on each questionnaire the caregiver completes. If diarrhea is present, further questions related to number of episodes will be asked. To obtain SAE and palpitation data, each questionnaire will contain open ended, non-symptom specific questions where caregivers can provide the study team with information about their child's illness or any other concerns they may have. Any response provided to this question will result in a trained study team member discussing the information provided in more detail via telephone. Any symptom or condition noted that meets the definition of an SAE (see Section 8.3.2) will be reported as outlined in Section 8.3.6.

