| Primary                                                                                                                                                                                                                                                                                                        |                                                                                                              |                                                                                                                                                                                                                                                                                                                                                                                                                                       |
| To determine if in previously healthy children, who present to an ED with gastroenteritis associated vomiting; is the proportion who develop moderate to severe disease [MVS ≥ 9] following ED evaluation significantly different in those who receive home ondansetron compared to those who receive placebo. | Post-index visit Modified Vesikari Scale (MVS) score in the 7 days following ED disposition  | The MVS is a composite measure which includes several aspects which represent the severity of disease. The score incorporates features of gastroenteritis that are of important to a variety of stakeholders including caregivers, children and physicians (e.g. duration of diarrhea and vomiting, frequency of diarrhea and vomiting, maximal height of fever, the presence of dehydration and the medical interventions required). |

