#### 9.4.2 ANALYSIS OF THE PRIMARY EFFICACY ENDPOINT(S)

The **primary outcome** for the study is a **post-enrollment (168 hours (7 days)) Modified Vesikari Score (MVS)**, defined as an MVS  $\geq 9$ . The post-enrollment score is calculated based on the elements of the score collected Day 0 through Day 7. Each of the seven components will be assigned a score for the entire study period (from ED disposition to Day 7). Scoring of each component is described in Table 3.0.

| Table 3.0 Modified Vesikari Scale                                       |          |                                     |                 |                      |
|-------------------------------------------------------------------------|----------|-------------------------------------|-----------------|----------------------|
| Scale Component                                                         | Score    |                                     |                 |                      |
|                                                                         | 0 Points | 1 Point                             | 2 Points        | 3 Points             |
| Diarrhea duration (hours)                                               | 0        | < 96.0                              | 96.0 – < 120.0  | $\geq 120.0$         |
| Maximum number of watery stools/24 hour period                          | 0        | 1–3                                 | 4–5             | $\geq 6$             |
| Vomiting duration (hours)                                               | 0        | < 24.0                              | 24.0 – < 48.0   | $\geq 48.0$          |
| Maximum number of vomiting episodes/24 hour period                      | 0        | 1                                   | 2–4             | $\geq 5$             |
| Maximum recorded rectal temperature ( $^{\circ}\text{C}$ ) † | <37.0    | 37.0 – < 38.5                       | 38.5 – < 39.0   | $\geq 39.0$          |
| Unscheduled health care visit                                           | None     | NA                                  | Primary care    | Emergency department |
| Treatment                                                               | None     | Rehydration with intravenous fluids | Hospitalization | NA                   |

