5. **Proportion of participants who require intravenous rehydration:** If the participant required an unscheduled health care visit (see #4 above), the participant will be asked additional questions related to intravenous (IV) insertion, treatment course, and disposition. Intravenous fluids administered at the index visit will not be included as part of this outcome.
6. **Caregiver satisfaction as measured by a 5-point Likert scale in the 48 hours following ED disposition:** Caregiver satisfaction with the therapy provided (oral ondansetron or placebo) in the 48 hours following ED disposition. This will be measured using a 5 point Likert scale on the questionnaire administered 168 hours after Time 0.

The analysis of secondary outcomes will be undertaken as detailed below:

1. **Frequency of vomiting from study enrollment to Day 7:** The total number of episodes of vomiting and diarrhea related to the presenting illness will be compared between groups (active and placebo) using a generalized linear model to compare differences between Poisson rates whilst adjusting for stratification.

2. **Duration of vomiting :** The total number of days the participant experiences vomiting from Day 0 to Day 7 will be compared using the Van Elteren test, stratified by center and duration of symptoms (pre-enrollment). If a number of patients still experience symptoms at the 7-day follow-up questionnaire, this will be tested using a suitable procedure to take account of censoring such as median regression or additive hazard models. Additional analyses involving this outcome will include linear regression models that adjust for possible effects of baseline characteristics.
3. **Proportion of participants who experience vomiting within 7 days of enrollment:** The proportion of participants with vomiting following enrollment will be compared using Mantel-Haenszel test stratified by site and weight.
4. **Proportion of participants who require an unscheduled health care provider visit within 7 days of enrollment:** The proportion of participants who require an unscheduled health care provider visit within 7 days of enrollment will be compared using Mantel-Haenszel test stratified by site and weight.

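### The outcome clock starts at consent in some sections and at ED disposition in others, for the primary MVS, the secondary vomiting outcomes and the diarrhea safety window

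*Combined protocol and SAP*

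**What the plan says.** **Primary MVS.** Section 3, on how the score is calculated, says "each variable is assigned a score for the entire study period (Time 0 to Day 7". The same section sets "Time 0 = consent date and time". It then says that the primary outcome "will ONLY include symptoms and outcomes that occur following the ED visit (i.e. after enrollment"), which treats the end of the ED visit and enrollment as one moment. Table 1.0 places the endpoint "in the 7 days following ED disposition". Section 9.4.2 says "Each of the seven components will be assigned a score for the entire study period (from ED disposition to Day 7"), although the sentence before it bases the score on "elements of the score collected Day 0 through Day 7".

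**Secondary vomiting outcomes.** The Synopsis and Table 1.0 ask about vomiting after ED disposition. Section 9.4.3 defines frequency from enrollment to Day 7 and the proportion within 7 days of enrollment. Its analysis item reads "The proportion of participants with vomiting following enrollment will be compared using Mantel-Haenszel test stratified by site and weight".

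**Diarrhea safety window.** Section 8.2 runs the 48 hours from randomization. Section 9.4.4 and Table 1.0 run the 48-hour frequency count from ED disposition.

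**Intravenous fluids.** For the secondary IV rehydration outcome, Section 9.4.3 says "Intravenous fluids administered at the index visit will not be included as part of this outcome". The MVS treatment rule (rule 7 in Section 9.4.2) deals with an admission directly from the index visit but says nothing about IV fluids at that visit.

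**The concern.** Consent, baseline data, randomization and dosing instruction all take place in the ED, so there is an interval between Time 0 and ED disposition. Children must have vomited within 6 hours of screening, so further vomiting in that interval is plausible. Study drug is given at home, no sooner than 8 hours after the clinical dose (Schedule of Activities, footnotes a and b), so it normally cannot have influenced those events.

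The start point therefore decides whether events before treatment count as outcomes. For the primary endpoint, two sections give different answers and neither is made subordinate to the other. For vomiting frequency and proportion, both in the Holm family of Section 9.4.1, the analysis section does not measure what the objective asks.

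**Working it through.** **1. Start points side by side**

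| Quantity | Starts at consent/enrollment or randomization | Starts at ED disposition |
|---|---|---|
| Primary MVS | Section 3, calculation paragraph (Time 0); Section 3, gloss equating the ED visit with enrollment | Table 1.0; Section 9.4.2, all seven components |
| Vomiting frequency and proportion | Section 9.4.3 (enrollment) | Synopsis and Table 1.0 objectives |
| Diarrhea, 48 hours | Section 8.2 (randomization) | Section 9.4.4; Table 1.0 |

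**2. One child under each reading.** Suppose a child vomits twice in the ED after consent and never again. On the Section 3 window, Table 3.0 gives 2 points for the maximum number of vomits (2–4 in 24 hours). Vomiting duration scores 0, because its own rule starts at ED disposition. On the Section 9.4.2 window the child scores 0 for both. In Section 9.4.3 the same child counts as having vomited; under the stated objective the child does not.

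**3. The plan's own figure.** Inputs from Section 9.2: 30% versus 20%, two-sided 0.05, 90% power. With pooled variance under the null and no continuity correction:

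n per arm = [1.960 × √(2 × 0.25 × 0.75) + 1.2816 × √(0.30 × 0.70 + 0.20 × 0.80)]² / 0.10² = [1.2002 + 0.7795]² / 0.01 ≈ 392, or 784 in total. This matches the plan, and nothing in this point changes it.

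**4. Illustration for the primary outcome, if the Section 3 window were used.** Let f be the share of children otherwise below 9 who reach MVS ≥ 9 only because of events before disposition, taken as equal in the two arms. The documents give no value for f; the range is an assumption. The observed rate is p + (1 − p)f, so the difference becomes 10 × (1 − f) points.

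| f (assumed) | Placebo | Ondansetron | Difference (points) | Power at 392 per arm |
|---|---|---|---|---|
| 0 | 30.0% | 20.0% | 10.0 | 90.0% |
| 1% | 30.7% | 20.8% | 9.9 | 88.8% |
| 2% | 31.4% | 21.6% | 9.8 | 87.6% |
| 5% | 33.5% | 24.0% | 9.5 | 83.7% |
| 10% | 37.0% | 28.0% | 9.0 | 76.8% |

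**5. The vomiting proportion as Section 9.4.3 defines it.** If a share q of children who do not vomit after disposition vomited only between consent and disposition, the same algebra multiplies any true difference by (1 − q). For assumed q of 5% to 15%, an assumed 10-point difference becomes 9.5 to 8.5 points. The documents do not give q either.

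**The case against.** The strongest reply is that the analysis section already settles the primary endpoint. Section 9.4.2 sets ED disposition for every component, its numbered rules sit under that sentence, and Table 1.0 agrees. This largely stands. A reader might infer that maximum vomits, maximum stools and maximum temperature have no start point because their own rules name none. The sentence governing all seven components supplies it. If Section 9.4.2 is followed and the data allow it, the MVS effect disappears.

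Three other stronger readings also go beyond the text.

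- A reader might infer that the 24-hour count blocks run from consent. Section 9.4.2 says only that the data come in 24-hour blocks. Section 3 says when caregivers are contacted, not what period they are asked about, and the questionnaire is not in the documents.
- A reader might infer that index-visit IV fluids will be scored in the MVS. Sections 3 and 9.4.3 ask caregivers about IV treatment only after a return visit, so the route described would not capture them. The silence in rule 7 is a gap to close, not evidence that these fluids will be scored.
- A reader might add up Table 3.0 points for vomits, fever and IV fluids and infer that ED events can carry a child most of the way to 9. The documents give no frequency for such combinations, so the sum says nothing about size.

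Nor is there a case for bias toward one arm: the events normally precede study drug in blinded, randomized groups.

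What the reply does not reach is the Section 3 wording, which nothing subordinates to Section 9.4.2, the secondary vomiting outcomes and the Section 8.2 window. For vomiting frequency and proportion the analysis section itself uses enrollment, so deferring to it settles the matter against the objective.

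**Conclusion.** The start points are inconsistent. In the primary endpoint the conflict lies between Section 3 and Section 9.4.2 with Table 1.0. For vomiting frequency and proportion, Section 9.4.3 as written counts vomiting in the ED after consent, contrary to the stated objective. Sections 8.2 and 9.4.4 disagree on the diarrhea window.

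The consequence is non-directional dilution and ambiguous scoring, of unknown and possibly small size. The power and difference figures above rest on assumed shares, taken as equal in both arms, and show only how the loss would scale. The figures of 784 evaluable and 1030 randomized stand. The point deserves correction because the rule decides how individual children are classified and the correction is mostly wording.

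**What to change.** Make ED disposition the single start point. Section 8.1 already has the ED disposition and the discharge date and time collected at chart review.

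- Section 3: replace the Time 0 window in the calculation paragraph, and the gloss equating the ED visit with enrollment, so that both match Section 9.4.2.
- Section 9.4.3: count vomiting frequency and proportion from ED disposition, in both the definitions and the analysis items.
- Section 8.2: align the diarrhea window with Section 9.4.4.
- Section 9.4.2, rule 7: state that IV fluids at the index visit are not scored, as secondary outcome 5 already does.
- Check that the 24-hour questionnaire's look-back matches this start point.

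The cost is mainly wording, with slightly fewer counted events in both arms. It may not be free for children already enrolled: Section 10.4 shows that recruitment was continuing at the November 2022 version. If the 24-hour count pooled ED and home episodes, knowing the disposition time may not separate them, and rewording the questionnaire partway would mix two definitions. The plan should state before unblinding how such counts are handled.
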